## Abstract

**Background:**

Depression is the second most important cause of disability worldwide. Reducing this major burden on global health requires a better understanding of the etiology, risk factors, and course of the disorder. With the goal of improving the prevention, recognition, and appropriate management of depressive disorders in China, the China Depression Cohort Study will establish a nationally representative sample of at least 85,000 adults (the China Depression Cohort Study-I) and 15,000 middle school students (the China Depression Cohort Study-II) and follow them over time to identify factors that influence the onset, characteristics, and course of depressive disorders. This protocol describes the China Depression Cohort Study-I.

**Methods:**

A multistage stratified random sampling method will be used to identify a nationally representative community-based cohort of at least 85,000 adults (i.e., ≥ 18 years of age) from 34 communities in 17 of mainland China’s 31 provincial-level administrative regions. Baseline data collection includes 1) demographic, social and clinical data, 2) diagnostic information, 3) biological samples (i.e., blood, urine, hair), 4) brain MRI scans, and 5) environmental data (e.g., community-level metrics of climate change, air pollution, and socio-economic characteristics). Baseline findings will identify participants with or without depressive disorders. Annual reassessments will monitor potential risk factors for depression and identify incident cases of depression. Cox Proportional-Hazards Regression, Network analysis, Disease trajectory modelling, and Machine learning prediction models will be used to analyze the collected data. The study’s main outcomes are the occurrence of depressive disorders; secondary outcomes include adverse behaviors (e.g., self-harm, suicide), the recurrence of depression and the incidence other mental disorders.

**Discussion:**

The China Depression Cohort Study-I will collect a comprehensive, nationally representative set of individual-level and community-level variables over time. The findings will reframe the understanding of depression from a ‘biology-psychology-society’ perspective. This perspective will improve psychiatrists’ understanding of depression and, thus, promote the development of more effective subgroup-specific antidepressant drugs and other interventions based on the new biomarkers and relationships identified in the study.

**Trail registration:**

The protocol has been registered on the Chinese Clinical Trial Registry (No. ChiCTR2200059016).

## Introduction

### Background

Depressive disorder was one of the top ten causes of disability-adjusted life-years (DALYs) lost worldwide in the 2019 Global Burden of Disease report [1]. The estimated global age-standardized prevalence of depressive disorders in 2019 was 3.1 ~ 3.8% [2]. Depression can occur at any age; the lifetime risk of depression is 15 ~ 18% [3]. Depression is a recurring disorder that is often treatment-resistant; 20 ~ 40% of patients treated for a major depressive disorder do not achieve remission after two or more courses of treatment with different antidepressants [4, 5]. Depression is an important risk factor for fatal and non-fatal suicidal behavior [6].

Reducing the global burden of depressive disorders requires a detailed understanding of the risk factors, biomarkers, course, and treatment responsiveness of the different subtypes of depression. Effectively using these findings to improve outcomes also requires detailed information about the community-specific identification, availability of treatment options, and care-seeking of persons with depression. A wide range of pathophysiological models and pathogenetic mechanisms have been proposed: the monoamine hypothesis, hypothalamic–pituitary–adrenal axis changes; inflammation; neuroplasticity and neurogenesis; structural and functional brain changes; genes; environmental milieu; and epigenetics (gene-environment interactions) [3]. No single model or mechanism can explain the complex interaction between external environmental factors and individual biological characteristics that regulates the onset and course of depressive disorders. Recent studies suggest that a variety of community-level environmental factors, such as air pollution [7, 8], green space exposure [9] and climate change [10], have significant associations with the onset and course of depression. But the mechanisms that regulate the interaction of these community-level factors with individual-level factors remain unknown [11]. Large longitudinal datasets that include community-level environmental factors and individual biological samples of community residents will be needed to clarify this relationship and, thus, understand the etiology of depression from the population level. We hypothesize that depressive disorders result from dynamic interactions among biological factors (e.g., genetic susceptibility), psychological characteristics (e.g., personal traits) and social-environmental factors (e.g., economic conditions, life events and climate change).

Understanding the dynamic relationships between environmental and individual factors that underpin depressive states require multi-faceted, longitudinal studies of large, representative samples. Such cohort studies are the best way to identify the incidence and natural history of diseases [12] and to simultaneously assess associations between multiple exposures and outcomes [13]. Several large cohort studies of depression have been reported, some following cohorts of community-based residents and others following cohorts of individuals with a history of depression. 1) A prospective birth cohort study in Brazil identified robbery in the prior 12 months as a risk factor for major depressive disorders [14]. 2) A population-based database from the UK Biobank found that patients with depression were more likely to have elevated levels of C-reactive protein (CRP), indicating low-grade inflammation; however, this relationship was no longer statistically significant after adjusting for smoking and BMI, suggesting that the presumed genetic contribution to increased inflammation in depression may be regulated by eating and smoking habits rather than a genetic predisposition [15]. 3) The Netherlands Study of Depression in Older Persons (NESDO) [16] followed a cohort of individuals with depression and reported that older age, early onset, severity of depressive symptoms, anxiety symptoms, comorbid anxiety disorder, fatigue, and loneliness were independent risk factors for late-life depression [17]. 4) The Netherlands Mental Health Survey and Incidence Study (NEMESIS) [18–20] followed a cohort of community residents 18–64 years of age and found that 12% of the subthreshold cases developed a depressive disorder during three years of follow-up. 5) The Australian Genetics of Depression Study collected questionnaire data and saliva samples from 20,689 participants (88% of whom met criteria for a lifetime depressive episode) to investigate the genetic architecture of depression and common comorbidities [21]. 6) The Uppsala Longitudinal Adolescent Depression Study in Sweden and the LIFE Child Depression study in Germany followed children and adolescents with depression until adulthood [22, 23]. And 7) some small-sample cohort studies investigated risk factors for depression in children with cancer [24], and in adolescents with sleep disorder [25].

Cohort studies about depression in China include small-sample studies focused on perinatal depression [26, 27] and large-sample studies that piggy-back on cohorts collected for other reasons such as The China Hainan Centenarian Cohort Study (CHCCS) and the China Kadoorie Biobank (CKB) study [28, 29]. These prior studies in China concentrated on the consequences of depression, not on the causes of depression. There is no nationally representative longitudinal cohort study of depression in China.

Most of the currently available cohort studies about depression have serious limitations. 1) The studies often include patients with depression at baseline, so they tend to focus on the outcomes of treatment rather than on the causes of the disorder. 2) Very few studies consider community-level environmental factors such as local impacts of climate change, level of urbanization, socio-economic status of the community, availability and quality of health services, and patterns of health-seeking behavior for mental disorders. 3) None of the available studies consider the role of dynamic interactions between community-level environmental factors and the characteristics of individual community members (such as genetic susceptibility, neural circuits and intestinal flora) on the onset and course of depressive disorders. And 4) few cohort studies propose or test predictive models about the mechanisms that result in depressive disorders.

The China Depression Cohort Study will address most of these limitations. It will recruit a representative community-based cohort of at least 85,000 adult individuals (the China Depression Cohort Study-I) and a school-based cohort of at least 15,000 middle school students 12 years of age or older (the China Depression Cohort Study-II). This report is a detailed protocol of The China Depression Cohort Study-I (hereafter referred to as “this study”).

### Aims

The primary objective of this study is to explore the etiology of depression from the ‘biology-psychology-society’ perspective. The specific aims are to 1) identify risk factors that influence the onset, severity, course and relapse of depressive disorders; 2) characterize distinct subtypes of depression; and 3) describe the mechanisms that regulate the interactions of environmental, social, psychological, and biological factors that are associated with the onset and course of depressive disorders.

## Methods and analyses

### Study design

This is a longitudinal prospective cohort study of a representative sample of community-dwelling residents in mainland China. The onset of episodes of depression in participants will be identified and the course of identified episodes will be monitored closely. Figure 1 shows the overall design of the project.

**Fig. 1 Fig1:**
[figure not shown]
Organization of the China Depression Cohort Study-I

### Study population

#### Sample criteria

Chinese citizens 18 years of age or older currently living in the selected communities who are registered permanent residents of the community (i.e., whose formal household registration is in the community) will be potential participants. Individuals who are transient residents, citizens of foreign countries, and persons living in institutional settings (chronic-care hospitals, boarding schools and universities, factories, prisons, etc.) will be excluded from the sampling frame.

#### Sampling method

We will use a multistage stratified random sampling method to identify 17 urban and 17 rural primary sampling sites in 17 of the 31 province-level administrative regions (hereafter, ‘provinces’) in mainland China. The 31 mainland provinces were first stratified by China’s seven administrative regions (Northeast, North, Northwest, East, Central, South and Southwest China) and then specific provinces from all seven geographic regions were selected to be nationally representative of the economic level and population size of the 31 different provinces. The 17 selected provinces included Heilongjiang and Liaoning from Northeast China; Beijing, Hebei, Tianjin, and Shanxi from North China; Gansu, Shanxi and Xinjiang from Northwest China; Zhejiang and Shanghai from East China; Henan, Hunan and Hubei from Central China; Guangdong from South China; and Sichuan and Chongqing from Southwest China.

Within each selected province, the second stage of sampling relied on China’s Disease Surveillance Points (DSP) System, a national representative sampling frame developed by the National Health Commission of the People’s Republic of China starting in 1978 that uses a stratified cluster random sampling method to select surveillance points (i.e., geographic areas that typically includes multiple communities or neighborhoods) around the country [30]. By 2021, a total of 605 points from all 31 provinces were included in this system, with a combined population of over 300 million individuals [30]. The disease surveillance points system provides a nationally representative cohort that has been widely used in national studies about the mortality and morbidity of various diseases [31, 32]. The number of DSP in the 17 selected provinces ranged from 7 (in Tianjin, Beijing and Shanghai) to 27 (in Heilongjiang). The DSP in each province were first stratified as urban or rural (based criteria specified by the National Bureau of Statistics) and then one urban and one rural DSP was selected for each province, resulting in a total 34 DSP. The criteria for selecting DSP within a province included 1) having a mean age of community members similar to that of all urban residents or all rural residents in the province; 2) having qualified mental health providers who were willing to participate in the management of the project; and 3) availability of MRI equipment needed to conduct the imaging part of the assessment.

Each DSP covered a variable number of specific communities, so the third stage of sampling was to select a single community within each of the 34 DSP where the project will be conducted. The criteria for selecting the 34 specific communities (‘primary sampling units’) included 1) having a mean age of community members similar to that of the entire DSP; 2) having a population of at least 3250 adults who are permanent residents (the minimum estimated sample required to enrolled 2500 adults); and 3) having local health institutions with sufficient human resources to perform the enrollment and follow-up procedures that are willing to participate in the project.

All permanent residents of the target communities meeting the inclusion and exclusion criteria will be eligible for inclusion in the cohort. Permanent residents meeting these criteria will be identified from the registers of residents in community health centers (which list virtually all permanent community members). Initially 3250 eligible individuals will be randomly selected from the lists of residents: after listing all adult eligible residents the total number of listed residents is divided by 3250 and the resultant integer and its fractional component (x.yy) are used to assess the proportion of the total list from which each x^th^ individual should be selected and the proportion of the total list from which each (x + 1)^th^ individual should be selected to arrive at a total sample of 3250. As many of these individuals as possible will be recruited into the project, even if the number of enrollees exceeds the minimum required sample of 2500 individuals. If contacting the 3250 eligible individuals does not result in enrolling 2500 individuals, an addition number of individuals from the resident list who were not selected the first time will be randomly selected in the same manner and invited to participate (considering the potential non-response rate of 30%, the additional number will be defined as 1.3 times of the differences between 2500 and actual number); this process will be repeated as needed until 2500 individuals have been enrolled. Reasons for non-enrollment and for post-enrollment drop-out will be described and the potential effects of selective enrollment and dropouts on the representativeness of the sample will be assessed by comparing the demographic characteristics of enrolled individuals with those of individuals who are selected for recruitment but not enrolled and of persons who drop out after enrollment with those of individuals who continue in the cohort.

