#### Data analyses

Three main analyses will be conducted. P values of < 0.05 will be considered statistically significant.

The first set of analyses will describe the characteristics of participants and the detailed epidemiology of depression, including the prevalence, incidence, regional characteristics, and trends in the demographic characteristics of depression over time. Means and standard deviations will be used to describe continuous variables, and numbers and percentages will be used to describe categorical variables. Poststratification weights will be used to estimate the national prevalence and incidence of depression. Latent variable analyses and disease trajectory analyses will be used to describe the changes of depressive disorders over time.

The second set of analyses will 1) identify risk factors that influence the onset, severity and course of depressive disorders; 2) identify characteristics that can help distinguish distinct subtypes of depression; and 3) assess potential pathophysiological mechanisms that link the different types of factors associated with depression – external environmental factors, social factors, psychological factors, and biological factors. T-tests, analyses of variance, Kruskal–Wallis tests and Chi-square tests will be used to analyze differences between groups. Correlation analyses will be used to check correlations between variables. To identify potential risk factors for depression, Cox regression analyses will be used to estimate the hazard ratios (HRs) of the association of specific bio-psycho-social risk factors with the diagnosis of depression. Logistic and liner regression will be used to identify factors associated with the severity or depressive episodes. Genomic analysis (including GWAS analysis, Mendelian Randomization), metabolomic analysis and gut microbiome analysis may also be used to explore potential biological mechanisms of depression.

The third set of analyses will use the findings about risk factors to generate and test different prediction tools of depression. Different predictive models will be generated using machine learning algorithms, including Support Vector Machine, Decision Tree and Random Forest algorithms [37, 38]. Performance of the different models will be compared using the area under the receiver operating curve, prospective prediction results (sensitivity, specificity, accuracy, positive predictive value, negative predictive value) and decision curve analysis (DCA) [38].

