The study also has some limitations. First, this study hasn’t covered every province, autonomous region and municipality in China. Second, the practicalities of identifying such a large cohort, conducting extensive evaluations of participants, and following participants for a minimum of 5 years required some trade-offs between the feasibility of conducting the project and the random selection of study sites. The selection of DSP within provinces and the selection of urban and rural communities within DSP was not strictly random, DSP and communities with very limited health care resources (that would be unable to manage the project) and communities with very small populations (that would not be able to recruit the minimum sample of 2500 individuals) were not included in the sampled DSP and communities. Third, the China Depression Cohort Study-I only considers depression among adults. The parallel China Depression Cohort Study-II will include middle school students 12 ~ 18 years of age, and we hope to subsequently expand the cohort to include children under 12 years of age and to continuously follow cohort participants of all ages.

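### The cohort is called a nationally representative random sample, but provinces, surveillance points and communities were chosen by criteria, so the planned national rates rest on an unstated modelling assumption

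*Protocol article*

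**What the plan says.** **The claim.** The Abstract (Methods) states: "A multistage stratified random sampling method will be used to identify a nationally representative community-based cohort of at least 85,000 adults". The Sampling method section opens in the same way: "We will use a multistage stratified random sampling method to identify 17 urban and 17 rural primary sampling sites". The Abstract's Background and Discussion also describe the sample or its data as nationally representative, and Study design calls the sample representative.

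**The procedure** (Sampling method, Sample criteria):
- Provinces: after stratification into seven regions, "specific provinces from all seven geographic regions were selected to be nationally representative of the economic level and population size".
- DSP: one urban and one rural point per province, chosen on mean age, on "having qualified mental health providers who were willing to participate in the management of the project", and on "availability of MRI equipment needed to conduct the imaging part of the assessment".
- Communities: one per DSP, chosen on mean age, a minimum of 3250 permanent adult residents, and willing local health institutions with enough staff.
- Individuals: random selection from the community's list of residents.
- Transient residents, foreign citizens and people in institutions "will be excluded from the sampling frame".

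**The planned use** (Data analyses): "Poststratification weights will be used to estimate the national prevalence and incidence of depression".

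**The disclosure** (Discussion, limitations): "The selection of DSP within provinces and the selection of urban and rural communities within DSP was not strictly random". The same paragraph says that areas with too few health resources to run the project, or too few people to fill the sample, were not included.

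**The concern.** A probability sample supports a national estimate because every unit in the target population has a known, non-zero chance of selection. Here that holds only for listed residents within a chosen community. Above that level no selection probabilities are known, and some areas had none at all. The limitations paragraph admits much of this, but the claim in the Abstract and Sampling method and the planned national estimates carry no qualification.

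At stake is the meaning of the national prevalence and incidence. The study is sized on the precision of a prevalence, so a reader will take the published interval as the uncertainty of a national figure. That interval would contain sampling error only. Any difference in depression between selected and excluded areas would lie outside it.

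**Working it through.** **1. Stages set side by side.**

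| Stage | How units were selected | Random draw described? |
|---|---|---|
| Province (17 of 31) | Region strata, then matching on economic level and population size | No |
| DSP (34) | Mean age, willing and qualified providers, MRI | No |
| Community (34) | Mean age, size, willing and staffed institutions | No |
| Resident | Drawn from resident lists | Yes |

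The only representativeness checks planned in Sampling method compare enrolled with non-enrolled people, and drop-outs with those who continue. Neither compares selected with unselected sites.

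**2. The plan's own precision figure.** Sample size gives n = 79,986 for a prevalence of 2.1% with a 95% interval of 2.0% to 2.2%. An exact (Clopper-Pearson) interval of full width 0.002 at p = 0.021 requires n = 79,986, which reproduces the figure. The simple normal formula, 1.96² × 0.021 × 0.979 / 0.001², gives about 78,977. Both treat the sample as independent random draws from the target population. The half-width of 0.1 percentage point has no component for selection of areas.

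**3. What weighting can and cannot do.** Let c be the share of the target population in areas that could be selected, and r the ratio of prevalence in excluded areas to prevalence in selectable areas, within weighting cells. If true national prevalence is 2.1%, the study estimates

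p_sel = 2.1% / (c + (1 − c) × r), and bias = p_sel − 2.1%.

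The bias is zero only if r = 1 or c = 1. The number of participants does not appear in the formula.

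**4. Illustration.** The documents give neither c nor r, so every value below is an assumption. Bias in percentage points:

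| c | r = 0.8 | r = 1.0 | r = 1.2 | r = 1.5 |
|---|---|---|---|---|
| 0.9 | +0.04 | 0 | −0.04 | −0.10 |
| 0.8 | +0.09 | 0 | −0.08 | −0.19 |
| 0.5 | +0.23 | 0 | −0.19 | −0.42 |

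For example, c = 0.8 and r = 1.5 give 2.1 / (0.8 + 0.2 × 1.5) = 2.1 / 1.1 = 1.91%, a bias of −0.19. A bias of −0.1 point needs 2.1 / 2.0 = 1.05 in the denominator, that is (1 − c) × (r − 1) = 0.05. With 20% of people in excluded areas this means r = 1.25. The table shows only how the bias behaves. It is not an estimate of it.

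**The case against.** The strongest reply is that the article is open about this. Every criterion is listed under Sampling method, and the limitations paragraph states the trade-off between feasibility and random site selection. This stands as far as it goes: nothing is hidden. But the paragraph does not repeat the willingness or MRI criteria, does not say that the provinces were chosen by criteria, and changes neither the claim nor the planned estimates.

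Several stronger readings are tempting, and the documents do not support them:
- A reader might infer that chance played no part above the resident level. Sampling method says the national DSP frame was itself built by stratified cluster random sampling. The 34 sites are a criteria-based subset of a randomly built frame.
- A reader might infer that weighting will use demographics alone, or that the results will be called design-based. Data analyses says neither and names no weighting variables, a detail an article may leave to an analysis plan. The difficulty with zero-probability areas does not depend on which variables are used.
- A reader might infer that better services inflate baseline prevalence through local recognition of depression. Baseline cases come from study screening and SCID-5-CV interviews. The argument has more force for incidence, because Follow-up also uses insurance records and self-reported treatment.
- A reader might take the restriction to registered, non-institutional residents as an error. It is a stated eligibility choice. It matters only because the national target population should be defined to match it.

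It is also fair to say that the primary objective is etiology and that national rates belong to the first, descriptive set of analyses.

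**Conclusion.** The point holds as a contradiction between the stated sampling method and the described one, with a consequence for national prevalence and incidence. Areas with no chance of selection can be represented by weighting only under the assumption that, within weighting cells, depression is the same there as in the selected areas. No planned analysis examines that assumption. Bias from its failure is not reduced by 85,000 participants and is not in the 2.0% to 2.2% interval.

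The size and sign of the bias cannot be derived from the documents. A reader might conclude from the illustration that it exceeds the 0.1-point half-width. Some assumed cases do, others do not, and r = 1 gives none. Within-cohort associations between risk factors and depression are less affected. The change is worth making, but the design as a cohort is not in question.

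**What to change.** 1. **Describe the sampling as it was done.** In the Abstract (Methods) and the opening sentence of Sampling method, state that provinces, DSP (from a randomly built national frame) and communities were selected by criteria, and that residents were randomly selected within communities. Qualify the representativeness of the cohort in the Abstract and in Study design to match the limitations paragraph. Where Sampling method uses the term for the DSP system, or for the provinces' economic level and population size, it need not change.
2. **Define the target and label the estimate.** In Data analyses, name the target population as registered, permanent, non-institutional adults, in line with Sample criteria, and weight to that population. Label national prevalence and incidence as model-based. Report a sensitivity range over assumed prevalence in the excluded areas, using the formula above or an equivalent, and treat incidence in the same way.
3. **Compare sites where data allow.** If area-level data are available, compare the selected DSP with unselected DSP in the 605-point frame. The documents do not show that such data are held, and one selected point per province and urban or rural stratum limits what can be learned. Calibration on these data is therefore optional.

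The cost is a less favourable headline claim and a little extra analysis. No new sites or participants are needed. Current status of the study reports only pilot work under way, so the change can be made before national figures are published.
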